### Data management

Each site has entered a standardized Participation Agreement with OBI to facilitate transfer of both raw and processed/de-identified data, in accordance with OBI’s Governance Policy and with any specific conditions required by each institution’s local legislative and/or ethical policies.

De-identified electronic data from all sites are aggregated for data analyses using multiple bioinformatics approaches. The OBI’s Centre for Ontario Data Exploration (“Brain-CODE”, https://www.braincode.ca/) is an online neuroinformatics platform that allows researchers to collaborate across distances and work more efficiently, and ultimately, to promote new discoveries to improve patient care. Brain-CODE provides the rare capability of supporting scientific inquiry and analytics across multiple brain diseases and modalities by integrating clinical, imaging, pathology, and genomics data. Standard variable definitions and formats are used so that investigators collect data consistently across studies and modalities. This will reduce variability in data collection and facilitate comparisons across diseases, merging of data sets and meta-analyses.

In storing sensitive patient information, Brain-CODE employs sophisticated security systems and utilizes Privacy by Design (PbD) to protect privacy by embedding it into the design specifications of technologies, business practices, and physical infrastructure [7]. The OBI also works with several research ethics boards and related organizations to streamline the project review and approval process; and develops opportunities to link or integrate Brain-CODE with other provincial, national, or international databases to augment its analytical power. With this unique complement of capabilities, Brain-CODE is the first database of its kind in the world.

Brain-CODE is deployed at the High Performance Computing Virtual Laboratory (HPCVL) data centre at Queen’s University in Kingston, Ontario. The HPCVL is a Compute Canada high-performance computing consortium that supports regulatory-compliant (e.g., ICH E6, 21 CFR Part 11, HIPAA, PIPEDA) processes for securing privacy of healthcare data [60]. All data are collected, processed, maintained, and stored in Canada.

Online data/images can be accessed only on secure websites via restricted portals requiring unique usernames and passwords for each member of the study team. User profiles are assigned only to study personnel requiring access to enter/verify data, and credentials for each user are vetted by the program manager.

Specific data-collection platforms with Brain-CODE include:Brain-CODE Subject Registry, a secure portal used by study centres in Ontario to link encrypted personal health information from study participants to provincial health/administrative databases;OpenClinica Enterprise, a regulatory-compliant, web-based electronic data capture (EDC) system and database for demographic and historical data, diagnostic information, and clinician-rated assessments and scales (OpenClinica, Waltham, MA, USA);LimeSurvey e-PRO Questionnaires, an open-source survey tool used by participants for direct entry of the 20 self-reported measures using a laptop or tablet while attending clinic visits (LimeSurvey, Hamburg, Germany);SPReD (originally the Stroke Patient Recovery Research Database), a comprehensive online repository powered by the open-source Extensible Neuroimaging Archiving Toolkit (XNAT) imaging informatics platform [61]. Structural and functional MRI data are first converted to DICOM (Digital Imaging and Communications in Medicine) format at each site prior to uploading [62], whereas EEG data are uploaded as raw files for subsequent standardization to 58 channels and conversion into a universally readable format in EEGLAB. Supplementary results, such as behavioural and physiological data, and session notes, are uploaded through a special sub-process. All files must be correctly labeled in accordance with SPReD’s organizational structure and naming conventions; an automated pipeline scans for errors on a daily basis; andBASE (BioArray Software Environment) and LabKey, open-source laboratory-information management systems that enable tracking and management of proteomics and genomics workflows, experiments, and raw data [63, 64].

Clinical data support is provided by Indoc Research for OpenClinica and LimeSurvey, and by Rotman Research Institute/Baycrest Health Sciences for SPReD. For clinical and self-rated measures, source data verification is completed using a remote, risk-based monitoring system that includes centralized processes for cleaning and extracting data. Future CAN-BIND projects (see below) will use secure, customizable Research Electronic Data Capture (REDCap) tools for all clinical and self-reported data [65].

MRI data undergoes manual quality control (QC) procedures where trained raters check for visual artifacts and then grade scans as usable or rejected; in the latter case, rescanning is recommended if possible within the study timeline. For fMRI data, preprocessing includes conversion from DICOM to NIfTI (Neuroimaging Informatics Technology Initiative) format [66] prior to identifying the volume with the least motion, to which the remaining volumes are registered.

Converted EEG data are resampled to 512 Hz with channels re-referenced to Cz before digital filters are applied (high pass = 0.5 Hz, low pass = 100 Hz) and trigger codes are standardized.

For a period following study closure, CAN-BIND data are protected by OBI for the exclusive use of the investigative team and its collaborators. However, in the future, de-identified CAN-BIND data may be shared by OBI with other collaborators and third parties for research purposes. These datasets could be made available to other clinical research teams with similar datasets for comparison of treatment outcomes in other psychiatric conditions (such as dementia, schizophrenia, and bipolar disorder). Eligible third parties will be recognized researchers or organizations who have submitted detailed study plans and ethics boards approvals to the OBI. Before OBI discloses the de-identified data to any third party, it will enter into an agreement with the latter to protect confidentiality and ensure correct usage of data.

### Analyses

We will examine several outcomes, including responders at Week 8 who maintained response at Week 16, responders at Week 8 who are non-responders at Week 16, non-responders at Week 8 who respond at Week 16 with augmentation, and non-responders at Weeks 8 and 16, among other outcomes. A reasonably large dataset is required to study adequately the complex clinical, neuroimaging, and molecular factors that contribute to treatment outcomes. Our sample size target for this phase of the CAN-BIND program is 200 patients and 90 healthy participants (290 in total).

To identify standalone features that differ significantly between responders and non-responders, either at baseline or over the course of the study, parametric two-sample t-tests will be used for features with normally distributed data. Otherwise, the non-parametric Mann–Whitney *U* test will be used. A significance threshold of α = 0.05 and multiple testing corrections will be required. Given an input list of up to 25,000 features, of which at least 250 are differentially expressed between responders and non-responders, assuming an overall false discovery rate of 5 %, and applying two-sample t-testing procedures, a minimum of 49 subjects per category are required for power of at least 90 % to correctly identify a given feature which differs significantly between the categories. If nonparametric testing procedures are used, a minimum of 52 subjects per category are required to achieve the same power. Target recruitment for patients with MDD is 200. An estimated response rate of 60 % would yield 120 responders and 80 non-responders. The planned sample size is sufficiently powered for both parametric and non-parametric univariate testing. Multivariate analysis and the development of prognostic signatures of escitalopram response will follow univariate analysis.

Data analyses will be conducted using a suite of commercial and open-source software tools installed on high-end workstations at HPCVL. While data from each analytical platform will be independently analyzed using the methods described above, important relationships (either correlational or causal) between modalities can be detected through an integration of data collected across assessment platforms for a given study subject.

To manage the integrated analyses of this complex data set, we have established a Data Science Advisory Team consisting of the Principal Investigators, domain-specific experts (e.g., molecular or imaging team members), informatics advisors, and operations support. This team will oversee processes for data cleaning, preprocessing, integration, quality control and overall analytics plans for each of the core research activities. Cross-domain as well as domain-specific data interrogation will be conducted by Working Groups responsible for applying specific analytic approaches according to their expertise and contributing to a master Statistical Analysis Plan. Conventional univariate and multivariate statistical approaches will address hypothesis-driven investigations, while a variety of analytics pipelines with both supervised and unsupervised techniques will allow exploratory analyses. Machine-learning approaches, including principle component analysis, random forests, and support vector machines will be used to identify subgroups of patients with shared symptoms and/or biological features that could have clinical relevance.

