### Treatments

In Phase 1, patients receive flexibly dosed escitalopram (10–20 mg/d) for 8 weeks. Patients are started at 10 mg/d and increased to 20 mg/d at Week 2 if they do not achieve ≥20 % reduction in MADRS score from baseline, and at Week 4 for those who do not achieve ≥50 % reduction in MADRS.

In Phase 2, patients who achieve ≥50 % reduction in baseline MADRS score at Week 8 are considered “responders” and continue on their effective dose of escitalopram for a further 8 weeks. Patients who do not achieve ≥50 % reduction in MADRS are considered “non-responders” and receive flexibly dosed aripiprazole (2–10 mg/d), added to escitalopram, for a further 8 weeks. Dose increases of aripiprazole are recommended if patients do not achieve ≥50 % reduction in MADRS after 2 or 4 weeks.

This standardized algorithm reflects usual clinical practice, is consistent with evidence-based treatment guidelines [11–13], and promotes consistency across all sites. Doses can be decreased at the discretion of the treating psychiatrist if patients do not tolerate higher doses. Treatment is open-label, and no randomization procedures are used. Medication adherence is monitored with pill counts at each visit.

Concomitant non-psychotropic medications for stable conditions are allowed at the discretion of the study psychiatrist, who can also permit use of vitamins, supplements, oral contraceptives, and non-prescription analgesics. Patients on pre-existing stable doses are allowed to continue on zopiclone up to 7.5 mg prn or lorazepam 1–2 mg prn, to a maximum of 3 doses/week.

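### The only univariate feature test the article details uses MADRS cut at 50%; the graded score should be analysed alongside it, and Phase 2 analyses conditioned on Week 8 MADRS

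*Protocol article*

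**What the plan says.** Under Treatments, "patients who achieve ≥50 % reduction in baseline MADRS score at Week 8 are considered “responders"; the rest are non-responders, and all of them have aripiprazole added for Weeks 8 to 16. Treatment is open-label and not randomised.

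Under Analyses, the univariate feature search is a two-sample t-test, or a Mann–Whitney test when the data are not normal, introduced by "To identify standalone features that differ significantly between responders and non-responders, either at baseline or over the course of the study". The error control is stated as "A significance threshold of α = 0.05 and multiple testing corrections will be required". The power statement begins "Given an input list of up to 25,000 features, of which at least 250 are differentially expressed between responders and non-responders", continues "assuming an overall false discovery rate of 5" per cent, and concludes that "a minimum of 49 subjects per category are required for power of at least 90" per cent (52 for the non-parametric test). With 200 patients and 60% response, the article expects 120 responders and 80 non-responders. Multivariate work and prognostic signatures come after this univariate step.

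The outcome list is four cross-classified categories. One is "non-responders at Week 8 who respond at Week 16 with augmentation", and the list ends "and non-responders at Weeks 8 and 16, among other outcomes". No feature test against the MADRS score itself is described, although the Clinical platform section has MADRS rated by structured interview. The Week 16 threshold and reference score are not restated.

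**The concern.** A two-group test treats a patient who improved by 5% and one who improved by 49% as identical, and patients at 49% and 51% as opposites. The graded information is discarded at the step that feeds the later multivariate work, in a screen of up to 25,000 features where the per-test threshold is strict. The study describes itself as having no preconceived biomarkers, so nothing in the article supports expecting only very large feature differences. Moderate features are the ones at risk of being missed.

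At Week 16 the issue is what the category means. If the 50% rule still refers to Week 0, a patient's distance from the line at Week 8 strongly affects the chance of crossing it by Week 16. A feature that tracks Week 8 severity could then look like a predictor of response to augmentation.

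**Working it through.** **Inputs from the article.** 25,000 features, of which 250 truly differ; FDR 5%; power 90%; 49 and 52 per category; 200 patients split 120/80; mean baseline MADRS 29.9 (Table 3, first cohort). The article gives no effect size and does not state whether tests are two-sided.

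**1. The article's own figure.** The per-test alpha implied by the FDR is (250 × 0.90 × 0.05) / (24,750 × 0.95) = 11.25 / 23,512.5 = 0.000478. With a two-sided t-test and an assumed standardised difference of 1.0, power is 89.4% at 48 per group and 90.3% at 49, so 49 reproduces. For the Mann–Whitney test, 49 × π/3 = 51.3, which rounds up to 52. At 120/80 the same test has 99.96% power for a difference of 1.0 and 90% for 0.70.

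**2. Efficiency of the cut.** For normally distributed MADRS change and a linear feature relation, efficiency relative to the continuous score is φ(z)² / [p(1 − p)], where p is the response rate and z the corresponding normal quantile.

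| Distribution | Response rate | Calculation | Efficiency | Loss |
|---|---|---|---|---|
| Normal | 50% | 0.3989² / 0.25 | 0.637 | 36% |
| Normal | 60% | 0.3863² / 0.24 | 0.622 | 38% |
| Normal | 70% | 0.3477² / 0.21 | 0.576 | 42% |
| Uniform | 60% | 3 × 0.60 × 0.40 | 0.720 | 28% |

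At 60% under normality, 200 patients carry the information of about 200 × 0.622 = 124.

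**3. Power for weaker features.** This compares a t-test on the 60/40 split with a correlation test on continuous change, at N = 200, alpha 0.000478 and without covariates. For r = 0.30:
- Cut: the implied standardised difference is (0.30 × 0.3863 / 0.24) / √(1 − 0.09 × 0.622) = 0.497. The non-centrality is 0.497 × √(120 × 80 / 200) = 3.44 against a critical value of 3.55, so power is 46%.
- Continuous: Fisher's z gives 0.3095 × √197 = 4.34 against 3.49, so power is 80%.

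Simulation agrees: 45% to 46% for the cut and 79% to 81% for the continuous score. Simulated values at other correlations:

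| Feature correlation | Cut | Continuous |
|---|---|---|
| 0.25 | 25% | 54% |
| 0.35 | 69% | 95% |
| 0.40 | 87% | 99% |
| 0.50 | 99% | 100% |

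**4. Week 16.** At a baseline of 29.9, one MADRS point is 100 / 29.9 = 3.3 percentage points. A patient at 48% improvement is 0.02 × 29.9 = 0.6 points from the line. How many crossings come from near the line depends on assumptions that the article cannot settle:
- Model A has no augmentation effect, equal Week 8 and Week 16 distributions, a Week 8 to Week 16 correlation of 0.5 to 0.9, and an SD of percentage change of 25 to 35. Between 17% and 40% of the 80 non-responders (14 to 32 patients) cross 50% anyway. Of those, 34% to 76% were within 10 percentage points (about 3 MADRS points) of the cut at Week 8.
- Model B takes Week 16 as Week 8 plus fluctuation with an SD of 3 to 7 points and a mean improvement of 0 to 9 points. Patients at 35% to 49% improvement at Week 8 supply 54% to 94% of the crossers, while making up 38% to 51% of all non-responders.

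**The case against.** **Response is the declared target.** The objective is to predict response, and the Week 8 cut also decides Phase 2 treatment, so it marks a real branch in care. This stands. It is a reason to keep the responder contrast, not a reason for it to be the only univariate test detailed.

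**The article leaves room for continuous analyses.** The outcome list is open-ended, and a master analysis plan, not shown, is to hold the detail. This stands in part: one can say only that this is the sole univariate feature test detailed here, not that no other is planned. But the test is a stated choice that the power calculation is built on, not a gap.

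**A reader might infer that the sample size is wrong or the study underpowered.** The documents do not support that. The 49 and 52 reproduce, and at 120/80 the test is amply powered for a difference of 1.0. The loss shows for smaller effects, which the article does not claim to target.

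**A reader might take 38% as a fixed property of the plan.** It needs normality, linearity and the 60% rate, and it concerns the Week 8 split only; the article gives no rates for the Week 16 categories.

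**A reader might infer that Phase 2 predictors would mostly identify who was near the line at Week 8.** That is too strong. The Week 0 reference at Week 16 is inferred from the Week 8 definition and the mention of maintained response. The near-threshold share falls as the assumed augmentation effect grows, and part of it only reflects how many non-responders sit in that band. Confounding also arises only for features that track Week 8 severity, and the calculations contain no features. Some of the difficulty is spontaneous change without a comparison arm, which no choice of outcome scale removes.

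**Conclusion.** The point holds in a limited form. The one univariate feature test detailed uses a dichotomised outcome where a graded one is at hand. Under normality, linearity and 60% response the cost is about 38% of efficiency, and 28% to 42% across the cases tried. The practical loss falls on features correlated roughly 0.25 to 0.35 with MADRS change; by a correlation of 0.50 it has almost gone. The stated power for the Week 8 split is unaffected.

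For Week 16, confounding of Phase 2 predictors with Week 8 severity is a real possibility if the rule is referenced to Week 0. Its direction is clear but its size is not established. The change is worth making because it is cheap, not because the stated analysis is invalid.

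**What to change.** - **Week 8 screen:** add, as a main analysis or co-analysis, a regression of Week 8 MADRS on each feature, adjusted for baseline MADRS and site and rank-based if the data are skewed, under the same 5% FDR control.
- **Phase 2:** among patients given aripiprazole, regress Week 16 MADRS on each feature, adjusted for Week 8 MADRS.
- **Responder contrast:** keep the 50% comparison as the clinically labelled analysis, and state which score Week 16 response is measured against.

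The cost is analysis-plan wording, one more set of FDR-controlled results, and some translation back to response rates for clinical readers. No new data are needed. The Phase 2 model addresses closeness to the line at Week 8; without a comparison arm it still cannot separate drug response from spontaneous change, and the report should say so.

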#### Neuroimaging platform

##### fMRI

Structural and functional neuroimaging data are obtained on 3.0 Tesla (3 T) magnetic resonance imaging (MRI) systems using multicoll phased-array head coils. Among the 6 clinical sites, 4 different models of scanners are used, thus mandating an extensive and ongoing standardization and quality control process to ensure that data are comparable and usable [44]. The four models of scanners include Discovery MR750 3.0T (GE Healthcare, Little Chalfont, Buckinghamshire, UK), Signa HDxt 3.0T (GE Healthcare, Little Chalfont, Buckinghamshire, UK), MAGNETOM TrioTim (Siemens Healthcare, Erlangen, Germany), and Achieva 3.0T (Philips Healthcare, Best, Netherlands). Cross-site T1 piloting included a “human phantom”, who travelled to each site for anatomical scans, and a manganese chloride (MnCl_2_)-based phantom model for progressive quantitative assessment of hydration based on signal intensity linearity characteristics [45]. Since the study’s launch, each site has obtained monthly scans of 2 geometric phantoms (a spherical agar phantom developed by the Function Bioinformatics Research Network, and a custom-built cylindrical model using plastic LEGO blocks) [46, 47] to facilitate scanner calibration and troubleshooting over the long term.

Following surveys and localization, the examination protocol includes a whole-brain T1-weighted turbo gradient echo sequence (9 min) at 1 mm^3^ resolution, repetition time (TR) = 6.2–1900 ms, echo time (TE) = 2.7–3.5 ms, flip angle = 8–15°, inversion time (TI) = 0–1100 ms, field of view (FOV) = 220–256 mm, matrix 256^2^–512^2^, 170–180 contiguous slices at 1 mm thickness. A small Vitamin E capsule is placed as a stereotactic marker at the right temple to confirm subject orientation during image review [48]. Secondly, a whole-brain diffusion tensor imaging (DTI) series is obtained using 30 gradient directions at 2 b-values (500 and 1000 s/mm^2^) (5 min) with an additional 3 images at b = 0 s/mm^2^ for tensor construction at a final voxel resolution of 2.3 x 2.3 x 5 mm (1 min). Functional MRI includes a 10-min resting state scan with eyes open using a fixation cross [49], obtained using a whole-brain T2*-sensitive blood oxygenation level-dependent (BOLD) echo planar imaging (EPI) series.

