##### Electroencephalography

The fMRI tasks were translated into analogous versions for electroencephalography (EEG), which is carried out at 4 sites, again using several equipment models (Biosemi ActiveTwo [BioSemi, Amsterdam, Netherlands], BrainVision Recorder/QuickAmp [Brain Products, Munich, Germany], Compumedics NeuroScan [Compumedics USA, Charlotte, NC, USA] , EGI Geodesic [Electrical Geodesics, Eugene, OR, USA]) that require cross-site consultation and standardization. All sites used a minimum of 64-channel caps and conductive electrode gels, with 53 common electrodes identified across the different systems. EEGs are digitized continuously (bandpass 0.04–100 Hz with 1000 Hz sampling rate) and all electrodes are referenced to the vertex (Cz) electrode.

At each session, participants complete a 10-min fixation resting state sequence with eyes open, followed by a 10-min resting state sequence with eyes closed. As with fMRI, the Emotional Face Categorization/Conflict Task was used for EEG when the study began, but was later changed to a task querying anhedonia in MDD and an affective go/no-go task, also using E-Prime software. Ocular artifacts, such as blinks, saccades, and lateral movements, are removed by independent component analysis (ICA) as implemented in EEGLAB [56] and performed using MATLAB (MathWorks, Natick, MA, USA).

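### The stated responder versus non-responder tests carry no site or scanner term, although MRI and EEG equipment differs by site; a site-adjusted test should replace them

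*Protocol article*

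**What the plan says.** The Analyses section of the protocol article names the test for standalone features that differ between responders and non-responders, at baseline or during the study: "parametric two-sample t-tests will be used for features with normally distributed data". "Otherwise, the non-parametric Mann–Whitney *U* test will be used". It adds: "A significance threshold of α = 0.05 and multiple testing corrections will be required". The same section says that the data of each platform are analysed by these methods, so MRI and EEG are included.

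The sample size starts from "Given an input list of up to 25,000 features, of which at least 250 are differentially expressed between responders and non-responders", a 5% false discovery rate and 90% power. It arrives at 49 subjects per category for the t-test and 52 for the non-parametric test. The planned 200 patients are expected to split into 120 responders and 80 non-responders.

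On equipment, the fMRI section says "Among the 6 clinical sites, 4 different models of scanners are used". The Electroencephalography section describes recording at 4 sites, "again using several equipment models". The article treats comparability as a matter of acquisition and data handling: travelling and geometric phantoms, visual quality control, common electrodes, resampling and filtering. Preprocessing, integration and analysis plans are assigned to a Data Science Advisory Team, and a master Statistical Analysis Plan is mentioned. No adjustment, stratification or harmonisation by site is stated.

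**The concern.** A two-sample t-test or Mann-Whitney test compares two pooled groups and has no place for site. If a baseline MRI or EEG feature keeps a site offset after standardization, two things can follow.

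- **Equal response rates across sites.** The offset is extra variance in both groups. The test remains valid but is less sensitive than one that removes site.
- **Response rates that differ by site.** The offset is associated with response. A feature that tracks the scanner can then appear to track response.

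The primary objective includes neuroimaging and electrophysiological predictors of response. A marker that reflects scanner or site would not carry over to other clinics.

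**Working it through.** **1. Reproducing the stated 49 and 52.** Inputs from the Analyses section: 25,000 features, 250 truly different, false discovery rate 5%, power 90%. Two-sided testing is assumed.

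Per-test alpha = (250 × 0.90 × 0.05) / (0.95 × 24,750) = 11.25 / 23,512.5 = 0.000478.

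Expected false positives = 24,750 × 0.000478 ≈ 12.

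The article gives no effect size. With a noncentral t distribution, noncentrality d × √(n₁n₂/(n₁+n₂)) and d = 1.0 SD, 49 per group gives power 0.903. For the rank test, 49 / (3/π) = 51.3, rounded up to 52. Both stated figures are thus reproduced with d = 1.0 SD and a variance that contains no site component.

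**2. Power of the plain t-test with a site component.** Assumptions: d is measured on the within-site SD, site explains a share ρ of total feature variance, and response rates are equal across sites. The effective difference is d × √(1−ρ), that is 0.894, 0.837 and 0.707 for d = 1.0 and ρ = 0.2, 0.3 and 0.5.

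| Groups, d | ρ = 0 | 0.1 | 0.2 | 0.3 | 0.5 |
|---|---|---|---|---|---|
| 49/49, d = 1.0 | 0.90 | 0.85 | 0.79 | 0.70 | 0.46 |
| 120/80, d = 1.0 | 1.00 | 0.999 | 0.995 | 0.987 | 0.908 |
| 120/80, d = 0.7 | 0.90 | 0.85 | 0.78 | 0.69 | 0.45 |

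The number per category needed for 90% power at d = 1.0 grows roughly as 49/(1−ρ): about 61, 70 and 98 at ρ = 0.2, 0.3 and 0.5. In simulation, a model with a site term kept power at 88–89% for d = 0.7 with N = 200.

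EEG is recorded at 4 of the 6 sites. If those sites contribute 4/6 of the 200 patients (assumption; about 80/53), power at d = 1.0 is 0.98 with no site variance and 0.87 at ρ = 0.3.

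**3. False positives.** Simulation of 200 patients at 6 near-equal sites, null features only, threshold 0.000478, scaled to 24,750 nulls (nominal about 12). Site response rates are assumptions, because the article gives none.

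| Site response rates | ρ = 0.2 | 0.3 | 0.5 |
|---|---|---|---|
| Equal, 60% everywhere | no inflation | no inflation | no inflation |
| Underlying 50–70% | about 23 | about 28 | about 53 |
| Underlying 45–75% | about 44 | about 74 | about 161 |

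With a site term the count stayed at about 9–14 throughout.

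"Underlying" means that chance variation in the realised rates comes on top. If the realised rates are exactly 45–75%, the plain test gives only about 24–37. If they are exactly 50–70%, it is conservative. Repeated runs of the underlying 45–75% case ranged over 44–55, 66–88 and 110–182, so these are orders of magnitude.

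If 250 × 0.90 = 225 true features are found, 44 false hits make a false share of 44/(44+225) = 16%, and 161 make 161/(161+225) = 42%, against 12/(12+225) = 5% nominally. These counts give every null feature the same site variance, so they are an upper illustration.

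**The case against.** The strongest reply is that this is a journal article. Covariates and harmonisation normally sit in the analysis plan, which is not shown, and a t-test on features already harmonised by site would fit the article's wording. That stands as a reason not to say that site will be ignored. It does not remove the point, because the article names a specific test for every platform, and a plan that adjusts for site would have to replace or qualify that statement.

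Three further objections limit the size:

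- Scanner and EEG models cannot affect blood assays or self-report scales. Specimens go to one biorepository under standard procedures, although a subset is analysed elsewhere. A constant site offset cancels in change from baseline. The exposure is therefore mainly in baseline MRI and EEG features.
- A common treatment algorithm and trained raters work against response rates that differ by site.
- The ranges of T1 settings in the fMRI section show that acquisition differs. They do not show how much of a feature's variance is due to site.

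Two stronger readings are tempting. One is that the 5% false discovery rate and the 90% power both fail as soon as scanner explains any variance. The calculations contradict this: equal response rates give no inflation, and at 120/80 with d = 1.0 power stays at about 0.90 or more.

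The other is that signatures will be built from features screened on all patients and then cross-validated on the same patients. The article says only "Multivariate analysis and the development of prognostic signatures of escitalopram response will follow univariate analysis". That gives an order. It describes no rule by which screened features enter the signatures, and no screening-then-cross-validation procedure, so the claim has no basis in the text.

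**Conclusion.** The point holds as a mismatch between a stated test and a documented multi-equipment design, chiefly for baseline MRI and EEG features.

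The power loss depends on an unknown site share of variance. It is marked at the stated minimum of 49 per category and for effects smaller than 1.0 SD. It is small at 120/80 for 1.0 SD unless site explains about half the variance. The 1.0 SD is inferred from the stated sample size.

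Inflated false positives need two conditions that the article neither states nor excludes: residual site effects, and response rates that differ by site. With underlying rates of 45–75%, roughly 45–160 false hits instead of about 12 is the upper illustration for site shares of 20–50%.

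This does not undermine the study. It is a correction worth making before analysis, because it costs almost nothing.

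**What to change.** - Replace the plain t-test with a linear model per feature that contains response group and site. Scanner model or EEG system may be used instead of site where that is the relevant unit.
- For non-normal features, use a site-stratified rank test (van Elteren) in place of Mann-Whitney U.
- State that the 49 and 52 per category assume either no site variance or a site-adjusted test.
- If the master Statistical Analysis Plan already adjusts or harmonises by site, say so, so that the stated tests are not read as the final analysis.

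The cost is 6 − 1 = 5 degrees of freedom for site (4 − 1 = 3 for EEG) and some wording in the analysis plan. No new data or visits are needed.
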